# Carbon ion reirradiation compared to intensity-modulated re-radiotherapy for recurrent head and neck cancer (CARE): a randomized controlled trial

**DOI:** 10.1186/s13014-020-01625-0

**Published:** 2020-08-05

**Keywords:** Head and neck cancer, Reirradiation, Toxicity, Local control, Particle therapy, Heavy ions, Squamous cell carcinoma, Intensity-modulated radiotherapy

## Abstract

**Background:**

Intensity-modulated re-radiotherapy (reIMRT) has been established as a standard local treatment option in patients with non-resectable, recurrent head and neck cancer (rHNC). However, the clinical outcome is unfavorable and severe toxicities (≥grade III) occurred in 30–40% of patients. The primary aim of the current trial is to investigate carbon ion reirradiation (reCIRT) compared to reIMRT in patients with rHNC regarding safety/toxicity as well as local control, overall survival (OS), and quality of life (QoL).

**Methods:**

The present trial will be performed as a single center, two-armed, prospective phase II study. A maximum of 72 patients will be treated with either reIMRT or reCIRT to evaluate severe (≥grade III) treatment-related toxicities (randomization ratio 1:1). The primary target value is to generate less than 35% acute/subacute severe toxicity (≥grade III), according to the Common Terminology Criteria for Adverse Events v5.0, within 6 months after study treatment. The total dose of reirradiation will range between 51 and 60 Gy or Gy (RBE), depending primarily on the radiotherapy interval and the cumulative dose to organs at risk. Individual dose prescription will be at the discretion of the treating radiation oncologist. The local and distant progression-free survival 12 months after reirradiation, the OS, and the QoL are the secondary endpoints of the trial. Explorative trial objectives are the longitudinal investigation of clinical patient-related parameters, tumor parameters on radiological imaging, and blood-based tumor analytics.

**Discussion:**

Recent retrospective studies suggested that reCIRT could represent a feasible and effective treatment modality for rHNC. This current randomized prospective trial is the first to investigate the toxicity and clinical outcome of reCIRT compared to reIMRT in patients with rHNC.

**Trial registration:**

ClinicalTrials.gov; NCT04185974; December 4th 2019.

## Background

Around 30–50% of patients with locally advanced head and neck cancer (HNC) develop local recurrence or tumor progression after initial multimodal therapy [1, 2]. Local tumor growth can lead to severe symptoms such as dysphagia, cachexia, and tumor pain with a significant decrease of the quality of life (QoL). The therapeutic options are limited in this highly pre-treated, vulnerable patient cohort. Depending on the tumor localization, salvage surgery should be evaluated in patients with good performance status with a 2-year progression-free survival around 70% for stage I/II and 30% for stage III rHNC [3]. However, only a subset of patients (approximately 30–50%) is suitable for a salvage surgery in the clinical routine. Palliative systemic therapies showed limited positive effects with the “EXTREME” regimen resulting in overall survival (OS) rates of 10.1 months and around 80% severe treatment toxicity (≥grade III) [4]. Recently, immunotherapy has emerged as a treatment option for patients with recurrent or metastatic head and neck squamous cell carcinoma (HNSCC) [5].

The clinical routine for reirradiation of rHNC is reIMRT [6, 7]. Definitive reIMRT is commonly applied with a total dose up to 60 Gy in 2 Gy fractions [8]. In this heavily pretreated patient cohort, reIMRT was associated with unfavorable rates of treatment-related toxicity (≥grade III) in 30–40% of patients [8–10]. The combination treatment of chemotherapy with photon reirradiation further intensified severe toxicities [6, 7] but showed unfavorable 2-year OS rates ranging from 15 to 26% in patients with rHNC. Stereotactic body radiation therapy (SBRT) has emerged as a viable therapeutic option for non-resectable rHNC with the potential to significantly reduce acute and chronic treatment associated toxicity [11, 12]. However, the clinical benefit of reirradiation with SBRT compared to reIMRT has yet to be demonstrated in a prospective clinical trial. High total doses from previous irradiation treatment generally limit the dose of reirradiation. The relative biological effectiveness (RBE) of carbon ions is higher compared to photons and it is associated with favorable effects in radioresistant tumors [13]. Because of the steep dose gradient, reCIRT is superior in sparing normal tissue and organs at risk, compared to reirradiation with photons. Consequently, carbon ions possibly represent a feasible and effective treatment modality for salvage reirradiation. A retrospective analysis on 229 consecutive patients with rHNC treated at our clinic with reCIRT showed encouraging results with 3.1% acute and 14.5% late severe (≥grade III) toxicity [14]. A median total dose of 51 Gy (RBE) in 17 fractions of 3 Gy (RBE) was safe and effective for reCIRT with a median OS of 13.7 months for patients with recurrent HNSCC. Data on reCIRT in patients with rHNC is rare, especially in the prospective setting. In the current CARE trial, the impact of reCIRT or reIMRT will be evaluated and the toxicity/safety and efficacy will be compared.

## Methods/design

The trial will be performed as a single-center, two-armed, randomized controlled phase II study. A maximum of 72 patients are projected to be enrolled into the study. Patients fulfilling the inclusion criteria will be treated with either reIMRT or reCIRT to evaluate severe (≥grade III) acute and subacute treatment-related toxicities (randomization ratio 1:1). Randomization will be stratified with respect to histology (HNSCC vs. others) and radiotherapy (RT) interval (≥2 years vs. < 2 years). Block randomization with varying block lengths will be performed. The overall duration of the trial is scheduled to be 60 months, consisting of 48 months of recruitment and a minimum follow-up of 12 months. A flow chart for trial subjects is shown in Fig. 1.

**Fig. 1 Fig1:**
[figure not shown]
Study flow chart for trial subjects. A total of 72 patients will be randomized (1:1) to the experimental arm A (carbon ions) or the control arm B (photons)

### Inclusion criteria

Inclusion criteria are as follows: Locally recurrent/progressive head and neck cancer after initial radiation therapy; microscopic or macroscopic tumor after salvage surgery; indication for reirradiation; completed wound healing after surgical intervention; Karnofsky Performance Score ≥ 60; age ≥ 18 years; written informed consent; ability of subject to understand character and individual consequences of the trial; for women of childbearing potential (and men), adequate contraception; and submission of previous RT records.

### Exclusion criteria

The exclusion criteria are as follows: Reirradiation of malignancy in the larynx; diagnosed plasymocytoma, sarcoma, or chordoma; previous reirradiation in-field; time interval < 6 months after initial RT; distant metastases (except pulmonary metastases); patients who have not recovered from acute toxicities of previous therapies; refusal of the patients to take part in the study; pregnant or lactating women; known carcinoma < 5 years ago (excluding carcinoma in situ of the cervix, basal cell carcinoma, squamous cell carcinoma of the skin) requiring immediate treatment that would interfere with the study therapy; and participation in another clinical study or observation period in a competing trial.

### Radiation therapy

Intensity controlled active raster scanning technology will be used for the application of reCIRT under image guidance with orthogonal X-rays and a daily position correction. A total of 17–20 fractions of 3 Gy (RBE) will be applied on 5–6 days per week, resulting in a total dose of reCIRT ranging between 51 and 60 Gy (RBE). According to standard procedures at our clinic, reIMRT will be performed under image guidance with daily computed tomography (CT) imaging and position correction. A total of 27–30 fractions of 2 Gy will be applied 5 days per week over a period of approximately 5–6 weeks using volume modulated arc therapy (VMAT). Elective nodal irradiation, which is associated with greater risk of acute toxicity, will not be performed.

#### Dose prescription

The total dose of reirradiation will range between 51 and 60 Gy or Gy (RBE) based on clinical experience in reCIRT of rHNC at our institution within the last 10 years [14]. Patients with an RT interval of less than 2 years will receive 51 Gy (RBE) reCIRT in 3 Gy (RBE) or 54 Gy photons in 2 Gy. Patients with an RT interval of over 2 years can receive up to 60 Gy (RBE) reCIRT in 3 Gy (RBE) or 60 Gy photons in 2 Gy. Additional factors influencing the dose prescription include the total dose of the initial course of RT, the patient’s performance status, initial tumor localization, the tumor volume to be treated with reirradiation, and previous salvage surgery. Individual dose prescription will be at the discretion of the treating radiation oncologist. The maximum total dose of reirradiation for selected patients equals 60 Gy or Gy (RBE). Details on the dose specifications are summarized in Table 1.

**Table 1 Tab1:** Dose specification for reIMRT and reCIRT

	CTV reIMRT	CTV reCIRT
Dose per fraction	2 Gy	3 Gy (RBE)
Total dose	54–60 Gy	51–60 Gy (RBE)
BED2Gy^a^	/	64–75 Gy

*Abbreviations*: *reIMRT* intensity-modulated re-radiotherapy, *reCIRT* carbon ion reirradiation, *CTV* clinical target volume, *RBE* relative biological effectiveness, *BED2Gy* biological effective dose in 2 Gy fractions, ^a^calculated according to the local effect model (LEM I) with an assumed alpha/beta of 2

The total dose will be prescribed to the maximum of the calculated dose distribution for the target volume. Treatment planning aims in the coverage of the clinical target volume (CTV) by the 95%-isodose-line for reCIRT and 90% coverage of the planning target volume (PTV) for photon plans. The relative biological effective dose of reCIRT will be calculated from the physical dose considering the local effect model LEM1 [13]. BED2Gy refers to the equivalent dose in conventional fractionation with 2 Gy fractions. As a precaution, the α/β value is uniformly set at 2 Gy, declaring the focus on organs at risk and the prevention of severe treatment-related toxicity. Target volumes of reCIRT will be defined as follows:

##### Gross tumor volume (GTV)

Tumor disease on planning CT scan, contrast enhanced CT scan or T1-weighted MRI.

##### Clinical target volume (CTV)

Adding 2–5 mm margin to the GTV including the resection cavity.

##### Plan target volume (PTV)

Adding 2–3 mm margin to the CTV depending on patient positioning and beam angles.

#### Organs at risk

Organs at risk such as the brain stem (α/β = 2), the optic system (α/β = 3), and the spinal cord (α/β = 2) will be contoured in accordance with clinical standards at our institution. Fractionation effects of particle therapy will be considered for cumulative dose calculation for organs at risk. Dose constraints for normal tissue and organs at risk in patients with an RT interval of less than 2 years will be respected according to Quantitative Analyses of Normal Tissue Effects in the Clinic (QUANTEC) [15, 16]. Approximate values for symptomatic necrosis of the brain, brainstem, spinal cord myelopathy, and optic neuropathy are listed as less than 3, 5, 1, and 3%, respectively, after RT [15]. Data on the tolerance of normal tissue and organs at risk for reirradiation are rare. Preclinical studies on reirradiation of rhesus monkeys suggest substantial recovery of the cervical spinal cord within 2 years after the initial course of RT [17]. At our institution, an increase of the dose tolerance of organs at risk in the second course of irradiation by 20% after 2 years has shown acceptable safety and treatment-associated toxicity in retrospective analyses [14]. Dose constraints of organs at risk will be closely guided by the clinical experience at our institution. The corresponding dose volume histograms for the organs at risk should not exceed the proposed values shown in Table 2.

**Table 2 Tab2:** Proposed radiation tolerance of organs at risk for reirradiation

	Maximum cumulative BED2Gy (RT interval < 2 years)	Maximum cumulative BED2Gy (RT interval ≥ 2 years)	Comment
Brain stem *(α/β = 2)*	60	78 (**≙** + 30%)	Maximum (surface)
Optic chiasm *(α/β = 3)*	54	64.8 (**≙** + 20%)	Maximum
Optic nerves *(α/β = 3)*	54	64.8 (**≙** + 20%)	Maximum
Spinal cord *(α/β = 2)*	45	54 (**≙** + 20%)	Maximum
Other organs at risk	ALARA*		/

*Abbreviations*: *BED2Gy* biological effective dose in 2 Gy fractions, *RT* radiotherapy, *ALARA* as low as reasonably achievable

In some cases, sparing of certain organs at risk (e.g. the ipsilateral optic nerve) is not feasible because of direct tumor infiltration. If neurological deficits are expected, because adherence to maximum dose constraints in the respective organs at risk is not reasonably achievable, the patient will be informed in detail. Should the patient accept respective impairments (e.g. vision loss) to achieve local tumor control, written documentation must be obtained before reirradiation. Treatment-related toxicities that occur as a consequence will be evaluated separately.

### Study endpoints

The feasibility/safety of reCIRT in patients with rHNC is the primary endpoint of the trial. The primary target value is to generate less than 35% acute/subacute severe toxicity (≥grade III) associated with study treatment within 6 months after reirradiation, according to Common Terminology Criteria for Adverse Events (CTCAE) v5.0. The local and distant progression-free survival 12 months after reirradiation, the OS, and the QoL are the secondary endpoints of the trial. Explorative trial objectives are the longitudinal investigation of clinical patient-related parameters, tumor parameters on radiological imaging, and blood-based tumor analytics.

### Study visits and evaluation criteria

The follow-up corresponds to the clinical routine and is not study-specific, with the exception of the QoL assessments. The first study visit will take place 6 weeks after reirradiation and thereafter every 3 months within the first year after reirradiation. Treatment response and progression will be defined according to the most recent Response Evaluation Criteria in Solid Tumors (RECIST) 1.1 [18, 19]. At the time of relapse after reirradiation, routine histological confirmation will be performed if clinically indicated (not study-specific). Detailed information on the study visits and evaluation criteria are shown in Fig. 2.

**Fig. 2 Fig2:**
[figure not shown]
Schedule of enrolment, interventions, and assessments for the prospective randomized controlled CARE trial (SPIRIT figure)

Patients will be followed-up for at least 12 months after reirradiation to document any acute and subacute CTCAE v5.0 toxicity that is related to study treatment. Patients with a partial follow-up are weighted by the proportion of the follow-up time that is completed. Acute toxicities are defined by the occurrence within the first 90 days after the start of reirradiation. Adverse events occurring after the first 90 days until 6 months after study treatment will be documented as subacute toxicities. Any adverse event emerging more than 6 months after reirradiation will be recorded as a late toxicity. Questionnaires used for QoL assessment will be the European Organisation for Research and Treatment of Cancer (EORTC) Quality of Life Questionnaire (QLQ)-C30 [20] and EORTC QLQ-H&N35 [21].

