#### Power calculation

Assuming a toxicity rate for the carbon ion arm of π_Tox_^CI^ = 0.35 under the null hypothesis, and a toxicity rate of π_Tox_^CI^ = 0.15 under the alternative hypothesis, it will be possible to reject H^0^: π_Tox_^CI^ ≥ 0.35 with a probability of 1-β = 0.803 with the planned sample size of *n* = 36 patients per arm, taking a potential dropout rate of 10% into account. Furthermore, assuming a toxicity rate of π_Tox_^Ph^ = 0.35 in the photon arm and π_Tox_^CI^ = 0.15 in the carbon ion arm, a difference between treatment arms can only be demonstrated with the planned sample size and a power of 1-β = 0.8 using a chi-squared test at the one-sided significance level of α = 0.15. A comparison at a one-sided significance level of α = 0.05 would have required a total of *n* = 146 patients (including dropouts), which was deemed to be an unfeasibly high number. The power calculation was done using SAS v9.4 (SAS Institute, Cary, NC, USA).

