#### Analysis of the primary endpoint

The null hypothesis for the primary (safety) endpoint of the trial is defined as H^0^: π_Tox_^CI^ ≥ 0.35 (i.e., the rate of patients with an acute/subacute toxicity CTCAE v5.0 ≥ grade III in the carbon ion arm is greater than or equal to 0.35), which is tested against its alternative H^1^: π_Tox_^CI^ < 0.35 (i.e., the rate of patients with an acute/subacute toxicity CTCAE v5.0 ≥ grade III in the carbon ion arm is less than 0.35). The null hypothesis will be tested at a one-sided significance level of α = 0.05 using an exact binomial test.

Furthermore, the toxicity rate will be estimated alongside a corresponding 90% exact Clopper–Pearson confidence interval. A (descriptive) comparison of the primary endpoint between the two treatment groups will be performed using a logistic regression model adjusting for histology (HNSCC vs. others) and RT interval (≥2 years vs. < 2 years), using a (descriptive) significance level of α = 0.15 (one-sided) for the odds ratio of the treatment group. The analysis of the primary endpoint will be based on the safety population, which comprises all patients enrolled who received at least one RT fraction.

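### The rule that weights patients by follow-up completed does not fit the exact binomial test of the primary endpoint, and can move the toxicity rate in either direction depending on how it is read

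*Protocol article*

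**What the plan says.** Under Study visits and evaluation criteria (text after Fig. 2), the article says "Patients will be followed-up for at least 12 months after reirradiation" in order to document acute and subacute treatment-related toxicity. The next sentence reads: "Patients with a partial follow-up are weighted by the proportion of the follow-up time that is completed". No analysis, denominator or exception is named.

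Under Study endpoints, the primary endpoint is severe acute or subacute toxicity within 6 months after reirradiation. Under Analysis of the primary endpoint, the carbon-arm rate is tested in the safety population (everyone with at least one fraction): "The null hypothesis will be tested at a one-sided significance level of α = 0.05 using an exact binomial test". The estimate comes with a "90% exact Clopper–Pearson confidence interval". That section mentions no weights.

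Under Power calculation, the toxicity rate is "0.35 under the null hypothesis" and "0.15 under the alternative hypothesis". With 36 patients per arm and 10% dropout, the null is rejected "with a probability of 1-β = 0.803".

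**The concern.** The exact binomial test and the Clopper–Pearson interval take a whole number of events among a whole number of patients. Weights between 0 and 1 give neither, so the two sections cannot both be followed if the weights enter the primary rate. This is the trial's only confirmatory test.

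Two features of the rule make its effect unpredictable:

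- **Denominator.** The endpoint window is 6 months, but the follow-up named just before the rule is 12 months. On a 12-month denominator, a patient who completes the whole endpoint window and dies at month 8 is still down-weighted.
- **Patients with events.** A patient whose outcome is already known to be a severe toxicity has nothing left to observe, yet the wording gives that patient a reduced weight if follow-up then ends, for instance through death.

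The safety conclusion could then depend on a choice of reading made after the data are seen.

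**Working it through.** **1. The plan's own power.** Inputs from Power calculation: null rate 0.35, alternative 0.15, one-sided α = 0.05, 36 patients, 10% dropout. 36 × 0.9 = 32.4, so 32 evaluable. The rule is to reject if X ≤ c, with c the largest count for which P(X ≤ c | 32, 0.35) ≤ 0.05. This gives c = 6, exact size 0.036 and power P(X ≤ 6 | 32, 0.15) = 0.805, against the stated 0.803. The stated power is therefore reproduced with whole, unweighted patients. With all 36 evaluable, c = 7, size is 0.033 and power 0.838.

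**2. A p-value for fractional counts.** None is defined in the plan. For illustration, the binomial tail is extended continuously: P = I₀.₆₅(W − X, X + 1), where I is the regularised incomplete beta function, W the sum of weights and X the weighted events. It equals the exact test when W and X are whole numbers.

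**3. Literal reading (events weighted too).** Take 8 events in 36 patients: 22.2%, exact p = 0.073, null kept. Suppose two of the eight are toxic deaths at week 6.

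| Denominator | Weight of each death | X | W | Rate | p |
|---|---|---|---|---|---|
| 6 months (26 weeks) | 6/26 = 0.231 | 6 + 2 × 0.231 = 6.46 | 34 + 2 × 0.231 = 34.46 | 18.8% | 0.030 |
| 12 months (52 weeks) | 6/52 = 0.115 | 6 + 2 × 0.115 = 6.23 | 34 + 2 × 0.115 = 34.23 | 18.2% | 0.026 |

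The null is now rejected. In simulation (36 patients, event times uniform over the window, 30% of patients with an event leaving follow-up at that event, and 0 to 30% of patients with unrelated partial follow-up), type I error was 0.075 to 0.099.

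**4. Other reading (only event-free patients weighted).** Take 7 events in 36: exact p = 0.033, null rejected. Suppose six of the 29 event-free patients die at month 8 and the denominator is 12 months. Each weighs 8/12, so W = 7 + 23 + 6 × 8/12 = 34. Then 7/34 gives p = 0.053 and the null is kept, although all six completed the 6-month window without an event.

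**5. Power under each reading.** Assumptions: exponential survival at the Background figure ("median OS of 13.7 months for patients with recurrent HNSCC"), toxicity onset within the first 3 months, true rate 15%. With λ = ln 2 / 13.7, deaths are 1 − exp(−6λ) = 26% by 6 months and 1 − exp(−12λ) = 46% by 12 months. The mean weight, (1 − exp(−λt))/(λt), is 0.862 or 0.750, so 36 patients weigh 36 × 0.862 = 31.0 or 36 × 0.750 = 27.0.

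| Who is weighted (36 treated) | 6-month denominator | 12-month denominator |
|---|---|---|
| All partial patients | about 0.77 | about 0.71 |
| Event-free patients only | about 0.69 | about 0.51 |

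These simulated values move by several hundredths with modelling details. If partial follow-up is instead unrelated to toxicity, affects 10 to 30% of patients, and events are spread evenly over the window, power is 0.83 to 0.81 with all partial patients weighted and 0.83 to 0.78 with event-free patients only.

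**The case against.** **The link to the primary test is inferred.** The sentence stands in a section on visits and names no analysis; the primary analysis and the power calculation are both written without weights. It might concern descriptive reporting only. This stands as a qualification. But the sentence directly follows the one on acute and subacute toxicity, which is the primary endpoint, and nothing confines it to description.

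**Weighting has a legitimate purpose.** Counting everyone with incomplete follow-up as a non-event also biases the rate. In the scenario with events spread evenly and 10, 20 or 30% unrelated partial follow-up, that approach gives type I error of 0.053, 0.080 and 0.119, against 0.039, 0.044 and 0.049 when all partial patients are weighted. This stands too. It means that removing the weights is not enough by itself; losses need a stated rule.

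**A reader might infer that the weighting removes the planned 80% power.** The documents do not support that. The 0.803 is correct for the unweighted test and already allows for 10% dropout. Starting from 32 patients and down-weighting them again would count losses twice, because the safety population can hold all 36. On the 6-month denominator their total weight is about 31, close to the planned 32.

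**A reader might also infer that early toxic deaths are certain to be shrunk while the rate is overstated as well.** These belong to mutually exclusive readings with opposite bias, and the document does not say which applies.

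**The survival input is approximate.** It is a retrospective median for the squamous-cell subgroup, the trial also admits other histologies, and the exponential form is assumed.

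**Conclusion.** The rule is wrong as written if it applies to the primary toxicity rate, as its placement suggests. It yields counts to which the planned test and interval do not apply, leaves its denominator open, and on its plain wording down-weights patients whose severe event has already been observed. Its effect can reverse the safety conclusion in either direction: p from 0.073 to about 0.03 with two early toxic deaths under the literal reading, or from 0.033 to 0.053 under the event-free-only reading with a 12-month denominator.

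The claim about power is narrower. The stated figure does not describe a weighted test, and power under weighting runs from about 0.5 to 0.8 depending on the reading. That range rests on the assumed exponential survival, early toxicity onset, 36 treated patients and the continuous extension of the binomial. The incompatibility with the exact test rests on none of these. The upward bias of the event-free-only reading depends on toxicity coming early or on the 12-month denominator.

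**What to change.** Remove the weighting from the primary analysis and state the following:

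- Every carbon-arm patient in the safety population counts once.
- Any qualifying grade III or higher event, including grade V, within the 6-month window is one full event, whatever the later follow-up.
- The primary handling of event-free patients who die within the window is named (for example as non-events, or with death as a competing event), separately from the handling of patients lost to follow-up. The two should not be merged, because silently treating losses as non-events favours rejecting the null.
- Two sensitivity analyses are added: losses counted as events, and the 6-month cumulative incidence with death as a competing event.

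If the weighting sentence was meant only for descriptive tables, it should say so and name its denominator. The cost is a few sentences and a little more analysis work; no additional data are needed.
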